1st day evaluation						
Sociodemographic data		X				
Clinical history		X		X	X	X
Weight and height	X	X		X		X
Body composition (dual-energy x-ray absorptiometry)						X
Accelerometry		X	X	X		
Physical fitness		X		X		
Nutritional study		X		X		X
Questionnaires to be fill there or at home between the 1st and 2nd evaluation days						
Low back-pain		X		X		X
Quality of life		X		X		X
Sleep quality		X	X	X		X
Physical activity		X	X	X		X
Self-perceived physical fitness		X	X	X		X
Sexual function		X		X		X
Restless legs syndrome		X		X		X
Mental and positive health		X		X		X
2nd day evaluation: Accelerometers collection and review of questionnaires		X		X		
Maternal biochemical analysis		X		X	X	
Umbilical cord blood sampling					X	
Maternal urine sampling		X		X	X	

Blood samples (5 mL) of all pregnant participants will be extracted at week 16th and 34th of gestation, and at delivery. Samples of venous and arterial blood from the umbilical cord (5 + 5 mL) at the time of delivery will be taken. In addition, samples of urine at 16 and 34 weeks gestation and delivery will be collected. All samples will be immediately frozen and conserved at −80 °C to avoid breaking the cold chain before being sent to the laboratory.

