## Exercise intervention

Most of exercise programs developed for pregnant women until now [20, 27, 52] have been designed in compliance with the recommendations of the American College of Obstetrics and Gynaecology (ACOG) in 2002 [53], or the Canadian Society for Exercise Physiology, among others [54]. However, in 2011, Zavorsky & Longo [55] launched a more actual, specific, and evidence-based guideline for exercise programs during pregnancy. Consequently, the exercise program that will be conducted in the present project has been developed accordingly to this guideline [55]. Nonetheless, we have also followed similar studies [56, 57] where aerobic and resistance training, as well as strengthening of the pelvic floor muscles [58], have been developed successfully and in line with these recommendations [57].

The exercise intervention (*n* = 30) will be performed in three groups of 10 participants and will meet the training standards of the American College of Sports Medicine [59] for adults. The groups will train 3 days/week (55–60 minutes per session) from the 17th week of gestation until delivery. The exercise sessions will be designed, carefully supervised, guided and instructed by qualified exercise professionals with experience in working with pregnant women.

The exercise program planning is shown in Table 3. The exercise intervention group will have different phases: a) *Information phase*: which will involve the understanding of the intervention plan for them, the goals we want to work with them, and how we will perform it (one training session); b) *Movement Learning phase*: theoretical and practical sessions with the explanation of movements and explanation of basic movement patterns (two training sessions); and c) *Physical Fitness Training phase*: with training sessions aimed at improving fitness and weight management (from the 18th until the 34th gestational week), and training sessions focused on a correct pelvic mobilization for the delivery (after the 34th gestational week until delivery) in order to try to reduce caesarean section rate, delivery time and number of pushes [23, 60].

**Table 3 Tab3:** Supervised exercise intervention program

SESION STRUCTURE	CONTENT										
WARM-UP 10 min	Joint mobility and different walk modalities										
CONDITIONING 40 min	Training week	1	2–4	5–6	7–8	9–10	11–12	13–14	15–16	17–18	>19
	Gestational week	17	18–20	21–22	23–24	25–26	27–28	29–30	31–32	33–34	>34

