To maximize adherence, several strategies will be implemented including music in all sessions and telephone calls following missed sessions. The researchers will control and register the presence of adverse events during the class and between classes.

The participants randomly assigned to the control group (*n* = 30) will receive general advices about the positive effects of PA during pregnancy for her and the foetus’s health status. The researchers will give three seminar explaining 1) the benefits of exercise for a better pregnancy, prevention and treatment of GDM and excessive weight gain; 2) ergonomic advises, exercises to perform at home (e.g. stretching, resistance training) and strategies to increase their daily PA levels; 3) the benefits of the Mediterranean Diet and nutritional education. Moreover, we will prepare brochures describing the overall benefits of PA on health, and we will dispense general guidelines to increase the level of daily PA and optimum nutrition during pregnancy [63, 64].

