### Secondary outcomes

#### Maternal and foetal outcomes

Birth weight; gestational age; type of delivery (natural, instrumental, or caesarean); Apgar scores (at 1 and 5 min); time of dilation, expulsion, and childbirth; GDM; and hypertension, will be obtained from perinatal obstetric records.

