##### Foetus/newborn

A monitoring of the evolution of the foetal anthropometrics will be performed by obstetrical ultrasound measurements following the standards of the International Society of Ultrasound in Obstetrics and Gynaecology guidelines and the methodology by Perin et al. [66]. The baby also will have a physical examination within 24 h after birth. Baby’s weight, length and head circumference will be measured. Newborns will be classified as having low birth weight or macrosomia when birth weight was less than 2500 g and greater than 4000 g, respectively.

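### The only stated rule for registering adverse events depends on attending classes, so events outside the shared data sources would be recorded in the exercise arm alone

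*Protocol article*

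**What the plan says.** The Exercise intervention section of the protocol article contains the only statement on registering adverse events: "The researchers will control and register the presence of adverse events during the class and between classes". It follows the adherence measures, which include "telephone calls following missed sessions", and comes just before the paragraph on the control group. The same section sets the class schedule: "The groups will train 3 days/week (55–60 minutes per session) from the 17th week of gestation until delivery".

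The control paragraph describes education and brochures: "The researchers will give three seminar explaining 1) the benefits of exercise for a better pregnancy", with two further topics covering ergonomics and home exercise, and diet. It mentions no registration of events.

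Several other sources make no distinction by arm. Under Maternal and foetal outcomes, a list of obstetric items ends with "GDM; and hypertension, will be obtained from perinatal obstetric records". Under Foetus/newborn, "The baby also will have a physical examination within 24 h after birth". Table 2 has a row for "Clinical history" marked at week 16, week 34, delivery and one month post-partum, and a low-back pain row marked at week 16, week 34 and one month post-partum.

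**The concern.** A count of adverse events can be compared between arms only if both arms are asked in the same way and equally often. Here the stated method is defined by an activity that one arm does not have. Controls also receive advice on exercising at home, including resistance work, so activity-related events are plausible in both arms.

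At stake is what the trial can say about the safety of a supervised programme in pregnancy that progresses to a perceived exertion of 15–16 (Table 3). Without control data, a reader could not tell whether a logged event reflects the programme or ordinary pregnancy. Events not asked about at the time are hard to recover later.

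**Working it through.** No figure in the article depends on this point, so the check sets the sources of harm information side by side, by arm.

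| Source (section) | Exercise arm | Control arm |
|---|---|---|
| Adverse-event registration (Exercise intervention) | During and between classes, three a week from week 17 to delivery | None stated; three seminars, no event registration mentioned |
| Obstetric records: birth weight, gestational age, delivery type, Apgar, labour times, gestational diabetes, hypertension (Maternal and foetal outcomes) | Yes | Same |
| Newborn examination within 24 h (Foetus/newborn) | Yes | Same |
| Clinical history (Table 2) | Week 16, week 34, delivery, one month post-partum | Same |
| Low-back pain by the Oswestry index and a visual analogue scale (Low-back pain; Table 2) | Week 16, week 34, one month post-partum | Same |
| Bodily pain within the SF-36 (Quality of life; Table 2) | Week 16, week 34, one month post-partum | Same |
| Week 24 assessment (Table 2) | Accelerometry and questionnaires; no clinical history | Same |

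1. **Which row differs.** Only the first. Within the exercise arm its coverage is complete in time, because during and between classes spans the whole programme up to delivery. The gap is between arms.

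2. **Which events depend on that row.** Remove everything collected alike in both arms: the obstetric-record items, newborn findings, low-back pain, SF-36 bodily pain, and whatever the clinical history elicits. What remains is events that no common source is stated to ask about, such as falls, injuries, and bleeding or contractions between visits. The article does not itemise the clinical history, so some of these may surface there, but nothing stated makes that happen.

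3. **What the plan does with the log.** The Statistical analysis section confines between-group effects to the primary and secondary outcomes. Registered adverse events are not among them, so no comparison of the log is stated. If one were made, it would set a running log against no corresponding record. If none is made, the events in step 2 have no comparator.

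4. **Whether a common occasion exists.** Table 2 already has four contacts after randomisation in both arms: week 24, week 34, delivery and one month post-partum. A common set of questions needs no new visit.

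**The case against.** The strongest reply is that the sentence describes programme monitoring. It sits with the adherence measures, does not say that events are registered nowhere else, and a condensed article may leave control-arm safety collection to the full protocol. In part this stands: the full protocol may hold a parallel procedure, and then one sentence in the article would settle the matter. It does not remove the point. The article goes beyond leaving a detail out: it states a rule, and that rule can be applied in one arm only.

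A second reply is that the main harms are covered without regard to arm and that outcome assessors are blinded. This is correct. A reader might infer that harms in general cannot be compared fairly in this trial. The documents do not support that: gestational diabetes, hypertension, delivery and newborn outcomes come from the same records in both arms, and low-back pain from the same questionnaires.

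A third reply is that no between-arm analysis of registered events is planned. This also stands. A reader might infer that the trial will make the programme look more harmful than it is; that would need a comparison the article does not state. Nor is a one-arm listing a fault in itself. The shortcoming is that nothing comparable stands beside it.

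Finally, a reader might be tempted to count classes against control visits, or to turn an assumed recall probability into an apparent rate ratio. Neither is sound. A class is not the same kind of contact as an assessment visit, and controls also have the seminars and the week 24 assessment. The article gives no detection or recall figure for either arm.

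**Conclusion.** The point holds in limited form. The one stated rule for registering adverse events applies to the exercise arm only. For events not captured by sources common to both arms, the trial as described would have data from one arm and no comparison. The size of any distortion cannot be calculated from the document. No primary or secondary outcome, planned analysis or sample-size figure is affected.

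This assumes that the article's sentence is the operative rule and that no parallel control-arm procedure exists in the full protocol. Unaffected here means collected alike. Which women enter the analysis of the record-based outcomes, given the analysis criteria under Table 1, is a separate question.

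**What to change.** - Ask the same short set of adverse-event questions in both arms at the contacts already scheduled: weeks 24 and 34, delivery and one month post-partum.
- State that any between-arm safety comparison uses those answers and the obstetric records only.
- Report the class log separately, as a descriptive listing for the exercise arm.
- If the full protocol already has such a procedure for controls, say so in one sentence.

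The cost is a short extra form at each of four existing contacts and a sentence or two of protocol text. No visit, sample-size or clinical rule changes. Brief questions at spaced contacts will miss some minor events that the class log catches, but they will do so by the same method and schedule in both arms, which is what the comparison needs.

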## Primary and secondary outcomes

### Primary outcome

The primary outcomes are maternal weight gain and maternal and foetal glycaemic profile. Maternal weight gain will be defined as the weight change from baseline measurement to the last measurement at 34th week of gestation. Maternal insulin sensitivity will be derived from the homeostatic model assessment for insulin resistance (HOMA-IR), which will be calculated using the formula [fasting insulin (μIU/mL) × fasting glucose (mg/dL)]/405 in the 34th week of gestation. Neonatal insulin sensitivity will be assessed through the cord blood ratio glucose/insulin.

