## Sample size

The number of participants to be included in the study was calculated on the basis of the change in body weight. We used the difference in weight change observed between the control and intervention group (1.04 Kg) in Ruiz et al. [20] as the expected effect size. A total of 52 women (26 per group) will be needed to detect a mean group difference of 1.04 and a standard deviation of 1.15 Kg in weight change with a power of 90 % and α of 0.05. However, we will exceed this sample size to allow for withdrawals. Assuming a maximum lost-to-follow up of 15 % [20], we will recruit a total of 30 participants per group (*n* = 60).

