## Statistical analysis

Since this study aims at determining potential biological effects of exercise, the statistical analysis will be performed on a per-protocol basis, thus, including in the analyses only participants who attended at least 80 % the exercise session and completed both baseline and follow-up evaluations. The treatment effects will be reported as between-group changes on the primary and secondary outcomes and will be assessed with generalized linear models after adjusting for baseline values. All the analyses will be repeated additionally adjusting for age and any other confounder potentially not well balanced at baseline, and the results from both models will be reported. The effect size (95 % confidence interval) and statistical significance will be reported for each study outcome. The statistical significance will be set at α = 0.05. Sensitivity analyses will be conducted using intention-to-treat analyses and baseline observation carried forward imputation.

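### Three primary outcomes are each tested at 0.05 with no order or alpha split, so if any one may count as a positive result the familywise error is about 14% under independence, not 5%

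*Protocol article*

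**What the plan says.** Under Primary outcome the protocol article states: "The primary outcomes are maternal weight gain and maternal and foetal glycaemic profile". Three measures follow. For the first, "Maternal weight gain will be defined as the weight change from baseline measurement to the last measurement at 34th week of gestation". Maternal glycaemia is measured by HOMA-IR at week 34. For the newborn, "Neonatal insulin sensitivity will be assessed through the cord blood ratio glucose/insulin". The Abstract lists the same set.

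The Statistical analysis section says "The statistical significance will be set at α = 0.05", and that "statistical significance will be reported for each study outcome". Treatment effects come from generalized linear models adjusted for the baseline value. The analyses are then repeated with age and any imbalanced confounders added, and both sets of results are reported.

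Under Sample size: "The number of participants to be included in the study was calculated on the basis of the change in body weight". The calculation allots 0.05 undivided to that one outcome. HOMA-IR and the cord ratio do not enter it.

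**The concern.** Three outcomes have equal primary status and each is judged against the same unadjusted threshold. Nothing in the article ranks them, divides the alpha or makes success depend on all of them. A reader of the eventual report could not tell whether a significant cord ratio with a null weight result is a positive trial. If it is, 0.05 is the error rate of each test and not of the trial's primary conclusion. The sample size section points the same way: with the full 0.05 spent on weight change, no alpha was set aside for the other two.

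**Working it through.** **Inputs.** From Sample size: difference 1.04 kg, SD 1.15 kg, power 90%, α 0.05, 26 women per group. From Primary outcome: three measures. From Statistical analysis: one level of 0.05 for every outcome. Sidedness is not stated, so two-sided is assumed; step 1 supports this.

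**Step 1: reproduce the plan's sample size.** By the normal approximation, n per group = 2 × (1.960 + 1.282)² × (1.15/1.04)² = 2 × 10.51 × 1.223 ≈ 25.7, so 26 per group and 52 in total, as stated. A one-sided test would need 21, which does not match. The t-test version gives 26.7, so 27 per group. The stated size is therefore a two-sided calculation on weight change with the whole 0.05.

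**Step 2: familywise error of the rule as written.** Suppose that exercise affects none of the three outcomes, that each test has its nominal size, and that any one significant result counts as positive.

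- Independent tests: 1 − (1 − 0.05)³ = 1 − 0.857375 = 14.26%.
- Upper bound under any dependence: 3 × 0.05 = 15%.
- Positive equicorrelation, from simulating three two-sided z-tests with 2,000,000 draws per value:

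| Assumed correlation | Familywise error |
|---|---|
| 0.2 | 14.0% |
| 0.3 | 13.6% |
| 0.5 | 12.6% |
| 0.7 | 10.9% |
| 0.9 | 8.4% |

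The document gives no correlations among the three measures, so these values are assumptions that show the range.

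If weight gain truly responds and only the two glycaemic outcomes are null, the corresponding figure under independence is 1 − 0.95² = 9.75%.

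**Step 3: compare remedies.**

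- *Bonferroni.* The level per test is 0.05/3 = 0.0167, and the familywise error under independence is 1 − (1 − 0.0167)³ ≈ 4.9%. With standardised effect 1.04/1.15 = 0.904 and 26 per group, t-test power for weight gain falls from 89.2% to 78.0% (normal approximation: 90.3% to 80.7%). Restoring 90% needs 34 (normal) or 35 (t-test) evaluable women per group.
- *Fixed sequence starting with weight gain.* Weight gain keeps 0.05 and its stated power. A later outcome is tested only after every earlier one is significant, so the familywise error stays at 5% whatever the correlations and whichever hypotheses are true.

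**The case against.** The strongest defence is that this is a condensed article and that a testing order often sits in the statistical analysis plan, which is not shown. Weight gain is listed first and is the only outcome that was sized, which is compatible with an intended order. Nor does the article say that one significant primary makes the trial a success.

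Part of this stands: the 14% depends on a success rule that the article leaves open. If all three outcomes had to be significant there would be no inflation, but the trial would then need power on all three. The defence does not remove the point, however. The article is not silent on alpha. It fixes one level, applies it outcome by outcome, and sizes the trial with that level undivided.

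Four stronger readings are tempting, and the documents do not support them.

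- *The two models double the number of chances.* A reader might infer this because both are reported. But the Statistical analysis section puts the baseline-adjusted model first and presents the other as a repeat, so main and supplementary is the natural reading. Naming the deciding model is a clarification.
- *The long biomarker list adds many false primary claims.* Those outcomes are secondary and do not bear on the primary error rate. A simple count would also mix plasma, erythrocyte and urine measures and count insulin twice.
- *The glycaemic primaries are underpowered.* No power is stated for them, but no variance or target difference is given either, so a shortfall cannot be shown.
- *14% is the maximum.* It is the independence value; the bound is 15%.

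**Conclusion.** The point holds in a conditional form. Under the rule as written, and if any one significant primary is taken as a positive result, the familywise error is about 14% under independence, at most 15%, and lower with positive correlation. That is two to three times the stated 5% for assumed correlations up to 0.7, and 8.4% at 0.9. The result assumes two-sided tests at their nominal size and no effect on any of the three outcomes.

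This should be fixed, but it is not a fundamental flaw. The three outcomes are few and named in advance, effect sizes with confidence intervals are promised for each, and the weight-gain calculation is sound at its stated level.

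**What to change.** State a fixed testing sequence: weight gain at two-sided 0.05, then HOMA-IR, then the cord ratio, each tested confirmatorily only if the one before it is significant.

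Name one deciding analysis per outcome:

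- For weight gain and HOMA-IR, the baseline-adjusted model.
- For the cord ratio, an unadjusted comparison between groups. Table 2 has cord blood sampled only at delivery, so there is no baseline value to adjust for.

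Label the additionally adjusted model supportive and the secondary outcomes exploratory.

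The change is wording only. It needs no more participants and costs weight gain no power, unlike the drop from about 89% to 78% under Bonferroni. The real cost is that HOMA-IR and the cord ratio can be reported only as estimates with confidence intervals, without a confirmatory claim, if weight gain is not significant. The order should be fixed before any outcome data are seen by group.

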### Secondary outcomes

#### Maternal and foetal outcomes

Birth weight; gestational age; type of delivery (natural, instrumental, or caesarean); Apgar scores (at 1 and 5 min); time of dilation, expulsion, and childbirth; GDM; and hypertension, will be obtained from perinatal obstetric records.

#### Blood pressure and resting heart rate

Systolic and diastolic blood pressure, as well as resting heart rate, will be measured after 5 min of rest, on 2 separate occasions (with 2 min between trials), with the person seated (Omron Health Care Europe B.V. Hoolddorp). The lowest value of the two trials will be selected for the analysis.

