## Randomization and blinding

After all the baseline evaluations, participants will be randomized to either the exercise intervention or the control group. A computer generated simple randomization sequence will be created before participants will be enrolled, to allocate participants to either group (1:1). The randomization sequence will be prepared by a member of the research team with no clinical involvement in the trial. The allocation will be concealed in a password protected computer file. Whereas the participants will be aware of their group allocation, outcome assessors and data analysts will be blinded to the allocation.

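### Analysing the lower of two readings for blood pressure and resting heart rate discards collected information and costs a modest amount of precision

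*Protocol article*

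**What the plan says.** The protocol article, under Blood pressure and resting heart rate, states: "Systolic and diastolic blood pressure, as well as resting heart rate, will be measured after 5 min of rest". The readings are taken "on 2 separate occasions (with 2 min between trials", with the woman seated. The section then fixes the summary value: "The lowest value of the two trials will be selected for the analysis".

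Under Recruitment process and measurements procedures, these measurements belong to the week 16 assessment, which is repeated in the same form at week 34. The rule therefore produces both the baseline value and the follow-up value.

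Under Statistical analysis, treatment effects are between-group changes that "will be assessed with generalized linear models after adjusting for baseline values". Under Randomization and blinding, "outcome assessors and data analysts will be blinded to the allocation".

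Nothing elsewhere in the article gives a reason for the minimum, replaces it with the mean, or adds the mean as a sensitivity analysis. The article itself fixes the rule, so it is not a detail left to an unseen analysis plan.

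**The concern.** Two readings are collected and one is thrown away according to its value. For a quantity that fluctuates around a resting level, the average of the pair uses both readings. The minimum adds noise, and it sits lower by an amount that depends on how variable the woman's readings are.

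The article also takes the best of two trials for handgrip and for the back-scratch test. There the target is maximal performance, so the rule has a purpose. Blood pressure and resting heart rate are not capacity tests, and the article does not say what quantity the lowest reading is meant to estimate.

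At stake is the precision of three secondary outcomes in a trial of 60 women. The primary analysis is per protocol, so fewer than 60 may contribute. Because the model adjusts for baseline, the extra noise enters both the covariate and the outcome.

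**Working it through.** **Inputs from the protocol article.** Two readings per visit; the minimum is analysed; the rule covers systolic pressure, diastolic pressure and resting heart rate; it applies at weeks 16 and 34; the model is baseline-adjusted. The article gives no blood pressure SD and no calculation for blood pressure, so there is no figure of the plan to reproduce on this point. Its one sample size calculation concerns weight change, and nothing below depends on it.

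**Assumptions.** The two readings at a visit are independent and normal around the woman's level μ with within-visit SD s (exchangeable readings). Illustrative values are s = 3, 5 or 7 mmHg with a between-woman SD of 8 mmHg.

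**Step 1: shift and error variance.** Let D be the difference between the two readings, so D has variance 2s². The minimum equals the mean of the pair minus |D|/2, and under normality the mean and D are independent.

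- Expected shift: E(|D|/2) = s/√π = 0.564s. The minimum lies 0.564s below the mean of the pair.
- Variance of the mean: s²/2 = 0.500s².
- Variance of |D|/2: s²(1/2 − 1/π) = 0.182s².
- Variance of the minimum: 0.500s² + 0.182s² = s²(1 − 1/π) = 0.682s².
- Ratio: 0.682/0.500 = 1.36. The minimum has 36% more within-visit error variance; its error SD is √1.363 = 1.17 times as large.

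A simulation of 2 million pairs agreed with these formulas.

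**Step 2: size on the outcome scale** (between-woman variance 8² = 64).

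| s (mmHg) | Shift 0.564s (mmHg) | Total variance, minimum | Total variance, mean | Ratio |
|---|---|---|---|---|
| 3 | 1.7 | 64 + 6.1 = 70.1 | 64 + 4.5 = 68.5 | 1.02 |
| 5 | 2.8 | 64 + 17.0 = 81.0 | 64 + 12.5 = 76.5 | 1.06 |
| 7 | 3.9 | 64 + 33.4 = 97.4 | 64 + 24.5 = 88.5 | 1.10 |

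Total variance is about 2%, 6% or 10% larger. Taking square roots, an unadjusted confidence interval is about 1%, 3% or 5% wider.

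**Step 3: with baseline adjustment.** Take a between-woman SD of 10 mmHg and a true correlation r between visits. With error variance v, total variance is T = 100 + v and the residual variance is T − (100r)²/T.

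- s = 5, r = 0.7: minimum 117.04 − 4900/117.04 = 75.2; mean 112.5 − 4900/112.5 = 68.9; ratio 1.09.
- s = 3, r = 0.5 gives 1.025; s = 8, r = 0.9 gives 1.235.

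The sample needed for equal precision therefore rises by about 2.5% to 23.5% over this range. The top needs both a large within-visit SD and a high between-visit correlation, and both are assumed.

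**Step 4: effect on the comparison between arms.** The expected spurious difference is (s₁ − s₂)/√π in absolute size, where s₁ and s₂ are the within-visit SDs in the two arms at follow-up. It is zero when they are equal. For 5 against 4 mmHg it is 0.56 mmHg; for 8 against 5 mmHg it is 1.69 mmHg. A change in variability between visits that both arms share does not enter the treatment effect.

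**Step 5: a first reading that runs high.** If the first reading is raised by 3 to 6 mmHg in every woman, simulation with s of 3, 5 or 8 gives an error variance ratio of 1.39 to 1.79. The minimum is noisier in every case tried. Distance from the settled level can go the other way: with s = 5 and a first reading 6 mmHg high, the bias is −0.8 mmHg for the minimum and +3.0 mmHg for the mean.

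**The case against.** A reader might infer that the minimum rule biases the treatment effect. The documents do not support that. The same rule applies to both arms at both visits, assessors and analysts are to be blinded, and the model adjusts for baseline, so a common downward shift cancels. Bias would need within-visit variability to differ by arm, and nothing in the article suggests that it does.

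A reader might also infer that the minimum is simply too low as a measure of resting pressure. That holds only if both readings share the same mean and that mean is the target. If first readings run high, the minimum can be the closer of the two. With s = 5 and a 6 mmHg excess, the mean squared error around the settled level is about 20.3 for the minimum (0.77² + 19.7) and 21.5 for the mean (3² + 12.5). With exchangeable readings the mean is clearly better, at 12.5 against 25.0. The article does not say which situation applies and does not offer a raised first reading as its reason. This objection stands as a limit on statements about absolute level. It does not rescue precision: a first-reading excess common to all women leaves the minimum noisier. The advantage of the mean would shrink or reverse only if the excess were large and also varied strongly between women, which nothing in the documents suggests.

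It is also fair that the minimum is a clear, prespecified rule that leaves no discretion. The primary outcomes and the sample size do not depend on it. Hypertension is taken from obstetric records, so this rule does not define it.

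**Conclusion.** The point holds as a modest loss of precision on three secondary outcomes. The 36% excess in within-visit error variance rests only on exchangeable, independent normal readings. The 2%, 6% or 10% increase in total variance rests on assumed SDs that the documents do not supply. Absolute levels would be reported about 1.7 to 3.9 mmHg below the mean of the same readings, under the same assumed within-visit SDs of 3 to 7 mmHg. No conclusion of the trial is invalidated. The reason to act is that the gain needs only data already being collected.

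**What to change.** Replace the sentence on the lowest value with one stating that the mean of the two readings is analysed for systolic pressure, diastolic pressure and resting heart rate at both week 16 and week 34, and that the lower reading is reported as a sensitivity analysis. The change concerns the analysed outcomes only and leaves the use of heart rate in the exercise prescription as it is.

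The cost is one sentence of analysis wording and one extra analysis per variable. No visit, reading or equipment is added. The small downside is that, if the first reading runs systematically high, the mean sits above the settled resting level, equally in both arms; the sensitivity analysis would let readers see how far the choice matters.
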